## **Study Design**

### Study Design and patient enrollment

The IMPROVE study is a randomized, controlled, cross-over trial to evaluate if intrathecal pump refills at home (Intervention) are better for patient comfort (Outcome) compared to intrathecal pump refills at the hospital (Control) in patients who receive IDD (Population). We will include at least 82 patients, who will each receive two refills in the outpatient clinic and two refills at home.

The physician will briefly explain the IMPROVE study to eligible patients. If the patient is interested, the researcher will explain the study concept and practical aspects of their potential participation. Additionally, the patients will be screened based on in- and exclusion criteria.

The researcher will explain the study to the patient, what's expected for them and what's in it for them. If the patient is positive about participation, IC and contact information will be provided. IC will be obtained on paper. After receiving a signed IC, the IC will be scanned and stored electronically after which the original paper version will be destroyed.

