### *Main analysis*

To evaluate and compare therapy effects, mixed model analysis will be used. The need for random intercepts and slopes will be assessed. Potential confounding variables, such as baseline stress and anxiety levels, will be taken into account in the analysis. Statistical as well as clinical significance differences will be defined at  $\alpha < 0.05$ . Additionally, based on baseline data, predictive modelling will be conducted to identify which patients will benefit the most from home-based refill procedures. This will involve the application of both supervised and unsupervised machine learning techniques (K-means clustering, decision trees, and Random Forest algorithms). All statistical analysis will be performed in SAS, SPSS and R.

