### *Health economic analysis*

A within-trial health economic evaluation will be conducted to assess the cost-effectiveness of home-based intrathecal pump refills compared to standard outpatient clinic refills. The analysis will include all participants, covering the period up to just before the third refill procedure. Each participant will receive one refill at home and one in the outpatient clinic, with a follow-up period of approximately 2–3 months between the refills.

The analysis will follow the intention-to-treat principle (79). Data on resource use will be collected through telephone interviews, as described in the outcome section ‘health expenditure’. The valuation of resource use will be based on official Belgian national tariffs.

Health outcomes will be assessed in two ways:

1. Percentage increase in comfort, as measured by the General Comfort Questionnaire, is the trial’s primary outcome.
2. Utility values, derived from EQ-5D questionnaires and converted using Belgian population-based value sets, in line with national health economic guidelines (55).

The outpatient refill procedure will serve as the control group. Any missing data will be addressed before analysis using appropriate methods for handling incomplete health economic data (79).

Cost differences between the two groups will be analyzed using generalized linear models. The Modified Park Test will guide the selection of the appropriate model specification (80). The main result will be the Incremental Cost-Effectiveness Ratio (ICER) (81), calculated with the estimation:

$$ICER = \frac{(\text{incremental cost})}{(\text{percentage increment in functioning})}$$

and

$$ICER = \frac{(\text{incremental cost})}{(\text{incremental QALY gained})}$$

To account for uncertainty, probabilistic sensitivity analysis will be conducted (79). Non-parametric bootstrapping will be used to assess variability in cost and outcome estimates. These results will be illustrated using Cost-Effectiveness Acceptability Curves (CEACs), showing the probability that the intervention is cost-effective at various willingness-to-pay (WTP) thresholds. All results will be reported in accordance with the Consolidated Health Economic Evaluation Reporting Standards (CHEERS) guidelines (82).

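### The within-trial cost comparison is worded as a two-group generalized linear model although every patient supplies both a home and a hospital interval; run as worded, its standard error would be too large

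*Protocol*

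**What the plan says.** Section 7.1 of the protocol describes a "randomized, controlled, cross-over trial" in which each patient has two home and two hospital refills. Section 7.2 groups the refills in pairs, one of each kind, to deal with time effects.

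The within-trial economic evaluation (section 10.4.3) runs up to just before the third refill, so it uses the first pair: "Each participant will receive one refill at home and one in the outpatient clinic". It continues: "The outpatient refill procedure will serve as the control group", and "Cost differences between the two groups will be analyzed using generalized linear models". The Modified Park Test is to guide the model specification. No patient term, clustering or interval term is mentioned. For uncertainty, "Non-parametric bootstrapping will be used to assess variability in cost and outcome estimates"; the resampling unit is not given.

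For the primary outcome, section 10.4.2 says "To evaluate and compare therapy effects, mixed model analysis will be used" and "The need for random intercepts and slopes will be assessed", with no criterion for that assessment.

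**The concern.** Section 10.4.3 describes two structures that do not fit together. If every participant contributes a home interval and a hospital interval, there are no two groups of patients; there are two conditions within each patient. A generalized linear model applied to two groups takes its standard error from independent records. Costs of the same patient in consecutive intervals are likely to be positively correlated, and the variance of a within-patient difference is then smaller than the model assumes.

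At stake is the stated precision of the cost difference, the numerator of the incremental cost-effectiveness ratio, which the section names as its main result. The cross-over earns that precision by design, and the wording gives it away.

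The primary model raises a related but smaller question. The design already dictates a patient effect, yet the text leaves both the intercept and the slope to an assessment of the data, so the error term of the primary test could depend on a preliminary test.

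**Working it through.** **Inputs.** Section 11.3 plans 82 patients with 20% loss: 82 × 0.8 = 65.6, so 65 or 66 complete patients. Section 10.4.3 states no cost variance, correlation or target precision, so it contains no figure to reproduce. The correlations, the gamma log-link form and the coefficient of variation of 1 below are assumptions.

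**Cost contrast, simple formula.** With n pairs, common variance s² and correlation rho, the mean difference has variance 2s²(1 − rho)/n. Treated as independent, it is given 2s²/n. The ratio of standard errors is 1/sqrt(1 − rho):
- rho 0.3: 1/sqrt(0.7) = 1.20
- rho 0.5: 1/sqrt(0.5) = 1.41
- rho 0.7: 1/sqrt(0.3) = 1.83

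**Cost contrast, model of the kind named.** Paired gamma costs were simulated with no true difference (66 pairs, coefficient of variation 1, 1,000 trials per correlation). A log-link gamma model with location as the only covariate was fitted.

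| Assumed correlation | Model SE / true SE | Type I error, pairing ignored | Type I error, patient-clustered SE |
|---|---|---|---|
| 0 | 0.97 | 6.0% | 5.5% |
| 0.3 | 1.14 | 3.1% | 6.5% |
| 0.5 | 1.34 | 0.9% | 6.3% |
| 0.7 | 1.60 | 0.2% | 7.6% |

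A second, separate simulation of a gamma log-link model with 66 pairs gave ratios of 1.17, 1.32 and 1.69 at 0.3, 0.5 and 0.7, with type I error of 2.1%, 1.2% and 0.3%. Together these give the range of about 15% to 65%.

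The ratios fall below the simple formula for two reasons. The correlation was set on a normal scale before conversion to gamma costs, which lowers the correlation between the costs themselves. The model standard error is also slightly small at zero correlation (0.97).

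With complete pairs the point estimate does not change; only its stated precision does. At a ratio of 1.34, 66 patients are credited with the precision of 66/1.34² = 37 in a paired analysis.

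**Primary model, intercept.** Take 66 patients with four refills and a 5% F-test of the patient variance. The statistic is scaled by 1 + 4·ICC/(1 − ICC), and dropping the intercept inflates the standard error by 1/sqrt(1 − ICC).

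| ICC | Chance intercept is kept | SE ratio if dropped |
|---|---|---|
| 0.05 | 25% | 1.026 |
| 0.10 | 58% | 1.054 |
| 0.20 | 96% | 1.118 |
| 0.30 | 99.9% | 1.195 |

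Where dropping is likely it matters little; where it would matter it hardly ever happens.

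**Primary model, slope.** Let r be the variance of the patient-specific home-minus-hospital effect divided by the residual variance. With two refills per location, leaving out a real slope multiplies the standard error by about sqrt((1 + r/3)/(1 + r)):
- r = 0.25: sqrt(1.0833/1.25) = 0.93
- r = 0.5: sqrt(1.1667/1.5) = 0.88
- r = 1: sqrt(1.3333/2) = 0.82

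Here the error is anti-conservative. With 65 completers, the slope kept only if F(64,130) is significant at 5%, and 200,000 simulated trials per setting, type I error was 0.054, 0.058, 0.060, 0.058 and 0.052 at r = 0.1, 0.2, 0.3, 0.5 and 1.0. Always keeping the slope gave about 0.050.

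**The case against.** The protocol nowhere says that the records are independent. It uses group and arm loosely for condition or order elsewhere (the summary, sections 7.2 and 7.3), always within an explicit cross-over, and a generalized linear model can be fitted by GEE or with clustered standard errors. This stands to the extent that the fault is conditional: it occurs if the section is followed as worded. It does not remove the contradiction, because the section settles how the model specification is selected and calls the outpatient condition a control group without any sign of a within-patient contrast.

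A reader might infer that the bootstrap is wrong and the acceptability curves too flat. The documents do not support that. The resampling unit is simply not stated, a statistical or health economic analysis plan may supply it, and resampling patients would preserve the pairing.

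A reader might also infer that the primary analysis has seriously inflated type I error. That would need the slope to be left out altogether, and the plan is to assess it. Section 10.4.2 does not even say whether the slopes refer to location or to time; the slope calculation takes them as location.

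Finally, the statement that "Potential confounding variables, such as baseline stress and anxiety levels, will be taken into account in the analysis" might be read as a design error, since baseline values do not vary within a patient. It is a matter of terminology: adjusting for baseline covariates does no harm here, and with incomplete patients some between-patient information enters the comparison.

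**Conclusion.** The point holds for the cost comparison. The text names a two-group model for data that it describes as paired. Carried out as worded, the standard error of the cost contrast would be about 15% to 65% too large at assumed correlations of 0.3 to 0.7. With no within-patient correlation there would be no such inflation. The direction is conservative: wider intervals and a test well below its nominal level, with no bias in the estimate and no false claim of savings. It concerns a secondary analysis, but one that the trial sets out to deliver.

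The primary-model point is real and small. A needed intercept would almost always be kept, and pre-testing a location slope costs at most about one percentage point of type I error.

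**What to change.** Reword section 10.4.3 so that the cost difference is a within-patient contrast between home and hospital intervals. Fit the generalized linear model by GEE, with patient-clustered standard errors, or with a patient random effect, and include a term for interval (first or second). State that the bootstrap resamples whole patients, so that both intervals' costs and outcomes stay together. Replace the references to two groups and a control group by two conditions.

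In section 10.4.2, state that the patient intercept and the patient-by-location effect are kept in the primary model whatever the data show.

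The change needs no new data, patients or procedures, and should be made before outcome data are seen. There are two modest costs. A retained slope loses a little precision if patients do not differ in their response to location. Clustered standard errors with a normal reference ran slightly liberal in the simulation at 66 pairs (5.5% to 7.6%; Monte Carlo error about sqrt(0.05 × 0.95/1000) = 0.7 percentage points), so a small-sample correction is advisable if that route is taken.

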#### Willingness-to-pay (WTP)

In addition to the cost-utility analysis, where QoL and life-years play a prominent role, a DCE will be conducted to estimate the WTP for pump refills at home. This preference elicitation method will help inform future reimbursement policy decisions by capturing the broader value that society places on the intervention (85).

A DCE is based on the idea that people's choices between different options depend on specific characteristics, or attributes, of those options. By systematically varying these attributes across scenarios and asking participants to choose between them, it is possible to estimate how much each attribute influences decision-making. This method will allow reverse engineer choice to quantify the impact of changes in attribute levels on choice. The results will complement the health economic evaluation by providing insight into preferences and perceived value from a societal perspective (86).

A literature review has been conducted to obtain the variables that represent the patient-centered values relevant to DCE (87-97). The following attributes will be used:

- Travel time and waiting time
- Person who performs the refill procedure
- Risk of wound infection
- Additional required amount that you should have to pay (non-reimbursed)

Each attribute is divided into multiple levels (Table 2, section 15). By combining different attributes and their corresponding levels, various scenarios can be created. These attributes will be presented in a choice set consisting of two scenarios (A and B), each representing different combinations of attribute levels (Table 2, section 15). Patients will be asked to choose between the two scenarios presented. During the study, patients will be asked to complete the DCE after the fourth refill. An example of such a choice set is shown in Table 3 (section 15).

## Ethical Considerations

### Ethical Conduct of the Study

#### Declaration of Helsinki

The trial will be performed in accordance with the Declaration of Helsinki, the conditions and principles of GCP, the protocol and applicable local regulatory requirements and laws.

#### Ethics Committee (EC)

Before the start of the trial or implementation of any amendment, approval of the trial protocol and amendments, ICFs and other relevant documents will be obtained from the applicable ethical committee.

An annual progress report will be submitted by the sponsor to the central EC within 30 days of the anniversary date on which the favorable opinion was given, and annually until the trial is declared ended.

Within one year after the end of the study, the investigator will submit a final clinical study report with the results, including any publications/abstracts, to the Sponsor, which in turn submits it to the central EC. The PI will notify the sponsor of the end of the study and the sponsor will notify the central EC of the end of the study. If the study is ended prematurely, the investigator will notify the central EC, including the reasons for the premature termination. All correspondence with the EC will be retained in the TMF/ISF.

#### Recruitment and Informed Consent (IC)

Eligible patients will only be included in the study after providing a written IC. IC will be obtained prior to conducting any study-specific procedures (as described in this protocol). These ICs will be collected on paper and then digitized, after which the paper versions will be destroyed.

Before enrolling in the study, the investigator will explain the study and the implications of participation to potential participants. Participants will be informed that their participation is voluntary and that they may withdraw consent to participate at any time. Participants will be told that their records may be accessed by CA and by authorized persons without violating the confidentiality of the participant, to the extent permitted by the applicable law(s) and/or regulations. By signing the ICF, the participant is authorizing such access.

After this explanation and before entry to the study, written, dated, and signed IC will be obtained from the participant. The ICF will be provided in a language sufficiently understood by the participant. Participants are given the opportunity to ask questions. The participant will be given sufficient time to read the ICF and to ask additional questions. After this explanation and before entry to the study, consent will be appropriately recorded by means of the participant's dated signature. After having obtained the consent, a copy of the ICF is given to the participant.

#### Sample size calculation

The sample size calculation (G\*Power version 3.1.9.4) is performed on patient comfort, measured with the general comfort questionnaire, as primary efficacy outcome variable after 4 intrathecal pump refill procedures. True mean comfort responses are based on the study of Zhao et al. (2021) (98), and a common standard deviation is calculated based on three studies which resulted in a value of 16.01049 (98–100). This results in an effect size of  $f=0.3035623$ . To conduct a randomized clinical trial with 2 intrathecal pump refill procedures at home and 2 procedures in the outpatient clinic with estimated true mean comfort responses for the outpatient clinic refill of 78.47 and 88.78 for the refill at home, with a common standard deviation of 16.01049, and 85% power to detect differences in means at a 5% two-sided significance level, a total sample size of 82 patients is needed. This sample size considers a 20% loss to follow-up after 4 refill procedures.

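### The effect size (f = 0.3035623) and the 85% power in the sample-size section do not fit the two-plus-two crossover; on the protocol's own inputs, power for 10.31 points is about 95% or more

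*Protocol*

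**What the plan says.** Protocol section 11.3 (Sample size calculation) takes the comfort questionnaire (GCQ) "as primary efficacy outcome variable after 4 intrathecal pump refill procedures". It assumes "estimated true mean comfort responses for the outpatient clinic refill of 78.47 and 88.78 for the refill at home". Both locations share one SD, 16.01049, and the section says that these inputs lead to f = 0.3035623. It concludes that for "85% power to detect differences in means at a 5% two-sided significance level, a total sample size of 82 patients is needed", and adds: "This sample size considers a 20% loss to follow-up after 4 refill procedures". G*Power is named, but not the test family, the number of groups or measurements, or a within-patient correlation.

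Section 7.1 gives the design: "The IMPROVE study is a randomized, controlled, cross-over trial", with at least 82 patients "who will each receive two refills in the outpatient clinic and two refills at home". Section 7.2 arranges the refills in home/hospital pairs, giving four tracks. Section 10.4.2 plans a mixed model.

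**The concern.** Each patient is observed at both locations, so the home-hospital effect is a within-patient contrast. Its precision depends on the correlations between a patient's scores, and section 11.3 gives none. The printed f also differs from the f that two equally weighted locations produce from the stated means and SD.

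What is at stake is whether section 11.3 justifies the sample size, because it is the only justification offered. If the stated power is not that of the trial, the reader cannot tell what size of difference 82 patients can detect. The statement that 82 are needed for 85% power would also be untrue on the protocol's own assumptions.

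**Working it through.** **Inputs (section 11.3).** Means 78.47 and 88.78, so the difference is 10.31. SD 16.01049. Two-sided 5% level, 85% power, 20% loss, N = 82. Two refills per location (section 7.1). Completers: 82 × 0.8 = 65.6, taken as 65.

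**1. Effect size**
- Standardised difference: d = 10.31 / 16.01049 = 0.64395.
- Two locations with equal weight: f = d/2 = 0.3220.
- Weights 1/3 and 2/3: f = d × √(1/3 × 2/3) = d × √2/3 = 0.3035623. This is the printed value to seven decimals.

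The printed f therefore does come from the stated means and SD, but under a 1:2 weighting.

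**2. Trying to reproduce N = 82.** Several settings land near 82:

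| Setting | N for 85% power | After the loss allowance |
|---|---|---|
| Between-patient factor, f = 0.3035623, 2 groups, 3 measures, correlation 0.5 | 68 | 68 × 1.2 = 81.6 |
| Between-patient factor, f = 0.322, 2 groups, 2 measures, correlation 0.5 | 68 | 68 × 1.2 = 81.6 |
| Between-patient factor, f = 0.3035623, 2 groups, 4 measures, correlation 0.5 | 64 | 64 / 0.8 = 80 |
| Within-patient factor, f = 0.3035623, 4 groups, 3 measures, SPSS-type noncentrality | 65 | 65 / 0.8 = 81.25, rounded up to 82 |

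The document does not allow a choice among these. A paired or default-option within-patient calculation gives 16 to 54 completers for correlations 0 to 0.5.

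**3. Power of the crossover contrast.** For each patient, take the mean of the two home scores minus the mean of the two hospital scores. Let r_s be the correlation between two refills at the same location and r_c that between refills at different locations.

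Variance of the contrast = SD² × (1 + r_s − 2 r_c)

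With one common correlation ρ (compound symmetry) this is SD² × (1 − ρ). With non-negative correlations it is at most 2 × SD² (r_s = 1, r_c = 0). Power is from the noncentral t distribution with n − 1 degrees of freedom.

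| Case | SD of contrast | Power for 10.31, 65 completers | Completers for 85% (enrolled, n/0.8) | Difference detectable with 85% power, 65 completers |
|---|---|---|---|---|
| ρ = 0.5 | 11.32 | >99.9% | 13 (17) | 4.3 |
| ρ = 0.3 | 13.40 | >99.9% | 18 (23) | 5.1 |
| ρ = 0 | 16.01 | 99.9% | 24 (30) | 6.0 |
| r_s = 0.5, r_c = 0 | 19.61 | 98.7% | 35 (44) | 7.4 |
| Worst case, r_s = 1, r_c = 0 | 22.64 | 95.1% | 46 (58) | 8.5 |

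**4. What 85% would require.** For power to fall to 85% with 65 completers, the SD of the contrast would have to be 27.3. The stated SD with non-negative correlations allows at most √2 × 16.01049 = 22.6. The conclusion therefore does not depend on the unstated correlation.

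**The case against.** **The effect size is not a slip.** It can be reproduced from the stated inputs, for instance with three cells of which two share the hospital mean. Baseline, hospital and home would be one such layout, since the protocol's summary plans a mixed model with baseline as a timepoint. It is also 6% below 0.322, which is the cautious direction. This stands as far as it goes: one might infer that f is unrelated to the means and SD, and that would be wrong. But section 11.3 does not mention such a layout, and this is not the f of the home-hospital comparison it describes.

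**The sponsor need not have sized a parallel-group trial.** A reader might infer this from the between-patient settings that land on 82. It is not established, since at least one within-patient setting also gives 82.

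**Power above 99% is not assured.** That figure needs compound symmetry. Two refills at the same location may well correlate more strongly than refills at different locations, and power then falls towards 95%. The SD also comes from outside studies and may not hold in this population. This stands, and it is why the result is given as a range.

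**The harm is limited.** The error is towards excess power. Allocation, analysis and type I error are untouched, and 82 is stated as a minimum. Even a trial with exactly 85% power can reach significance with an observed difference smaller than planned. All of this stands and lowers the severity, but it does not make the stated power right.

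**Conclusion.** The point holds as an error in stated figures. For the design described, f is 0.322, and 0.3035623 rests on an unexplained 1:2 weighting. The power of 82 enrolled patients (65 completers) for 10.31 points is about 95% in the worst case with non-negative correlations and 99.9% or more under compound symmetry, not 85%. For 85% power, 24 completers are enough at correlation 0, 13 at correlation 0.5 and 46 in the worst case.

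These figures assume that 16.01049 is the SD of a single GCQ score, that correlations are non-negative and that there is no carry-over.

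A reader might infer that the primary test is endangered or that enrolment must be cut. The documents support neither: the trial is more than adequately powered for its planned difference, and the number may also serve secondary or economic objectives, although section 11.3 does not say so. This is a correction to make in the protocol, of moderate rather than critical importance.

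**What to change.** Rewrite section 11.3 as a within-patient calculation and keep N = 82:

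- Correct f to 0.322 or give the equivalent paired effect size; otherwise explain the 1:2 weighting.
- Name the test family, the number of groups and the number of measurements.
- State the assumed same-location and cross-location correlations.
- Replace the 85% claim with what 82 enrolled (65 completers) deliver: at least about 95% power for 10.31 points. Equivalently, 85% power for about 4.3 points (correlation 0.5) to 6.0 points (correlation 0) under compound symmetry, and for about 8.5 points in the worst case.
- If 82 rests on the secondary or economic objectives, say so.

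The cost is protocol wording only. Enrolment, randomization and analysis do not change.
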